### Adverse Events

Any adverse event caused by antibiotic (12), FMT therapy, study food intake, blood sampling, and endoscopy should be recorded in detail, including symptoms, time, duration, and follow-up until complete resolution or termination of treatment. If there is any serious adverse event that may lead to death, life-threatening, or intolerability, the study will be terminated and treatment will begin immediately.

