**Methods and Analysis:**

This trial is a double-blinded, randomized, placebo-controlled, parallel assignment trial. Patients with UC and fecal donation candidates will undergo strict screening before being involved in the trial. Eligible patients are randomly divided into two groups: one group will drink one bottle of alginate twice a day for 8 consecutive weeks after A-FMT, while the other group will take a placebo instead of the alginate drink. The primary endpoints are the changes in the Total Mayo Score at 8 weeks after study initiation and A-FMT from baseline. The secondary endpoint is the comparison of clinical features, microbiota, and metabolomic analysis before and after 8 weeks of study food intake. Changes at 6, 12, 18, and 24 months after A-FMT will be assessed. Finally, a subpopulation analysis of the relationship between patients and donors is an exploratory endpoint.

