### Interventional Methods

First, eligible patients with UC will receive a combination antibiotic regimen called AFM comprising oral amoxicillin (1,500 mg/day), fosfomycin (3,000 mg/day), and metronidazole (750 mg/day). AFM will be administered to patients for 2 weeks until 2 days before the FMT (15). The fecal suspension (200 ml) will be thawed at 37°C using a water bath shaker on the day of the FMT operation. After bowel lavage using a standard polyethylene glycol (PEG) solution (Moviprep; EA Pharma, Tokyo, Japan), the patients will undergo total colonoscopy. A total of 200 mL of fecal suspension will be transferred to the patient's cecum. After the procedure, patients will receive scopolamine (10 mg) to slow intestinal transit and maintain a right lateral position. If the patient's drug dose for UC treatment has been stable for at least 12 weeks before the pre-registration, the patient will be permitted to continue ongoing treatment. However, changes in the dosage of drugs or initiation of new treatments will not be allowed during the intervention. After the A-FMT regimen described above, the patients will be randomized into two groups for a double-blind FMT post-treatment. One group will consume one bottle of alginate drink twice a day for 8 consecutive weeks, while the other group will take a placebo. The alginate drink is a mixed tea drink provided by Kaigen Pharma Co., Ltd. (Osaka, Japan) containing 4 g of sodium alginate per bottle (150 g) and has been proven to be safe (https://www.h-food.or.jp/dbadm/media/231cec6ad1478e2d429f733d93a7b272.pdf). The placebo uses the same tea drink with the sodium alginate removed and does not have a different appearance or taste. Patients can adjust their medication during post-observation after the study food intervention. To compare the effects of treatment, all patients will undergo symptom checking and colonoscopy and have blood and fecal samples tested at the times indicated in Table 3. Colonoscopy founding at screening, A-FMT and 8 weeks after study food intake should be taken video and judged by a third-part expert to confirm the scope and severity of UC lesions. Biopsy of inflammatory sites will be used to evaluate the histological score. Blood samples will be used to test routine blood biochemistry, and plasma components will be separated by centrifugal force and cryopreserved at −60°C. Fecal samples will be collected to determine the occult blood condition and calprotectin levels and analyze the intestinal microbiota and metabolites.

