
**Table 3 T5:** Protocol for sequential therapy of A-FMT with alginate drink or placebo.

[figure not shown]	**Screening stage**		**Duration of administration**				**Post-observation**
	**Pre-registration (within 2 months)**	**Screening (within a month)**	**AFM**	**A-FMT**	**Alginate drink or Placebo**		**6, 12, 18, and 24 months after**
			**2 weeks**		**4 weeks after**	**8 weeks after**	
Informed consent	•						
Check of patient background	•						
Administration of study food					•	•	
Check of symptoms	•	•		•	•	•	•
Endoscopy		•		•		•	
Blood samples		•		•		•	•
Fecal samples		•		•		•	•

*A-FMT, FMT following triple antibiotic therapy AFM (amoxicillin, fosfomycin, and metronidazole)*.

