### Randomization

Eligible patients will be randomized at a ratio of 1:1 using an Interactive Web Response System (REDCap: Research Electronic Data CAPture). The simple randomization is carried out by the staff in charge of the clinical research and trial Center of the Juntendo University Hospital to ensure concealment of allocation. The medical staff, assistants and patients of our study team did not know the condition of random allocation until the experiment was completely finished.

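### The protocol conditions adverse-event recording on a causal judgement, which leaves the safety record incomplete and less sensitive to a difference between arms; the end of event follow-up is also ambiguous

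*Protocol article*

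**What the plan says.** The Adverse Events section is the only text in the article on recording harms. Its rule is: "Any adverse event caused by antibiotic (12), FMT therapy, study food intake, blood sampling, and endoscopy should be recorded in detail". A recorded event then has "follow-up until complete resolution or termination of treatment". The section does not say whether the treatment meant is the study treatment or the treatment given for the event.

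The next sentence deals with serious events: "If there is any serious adverse event that may lead to death, life-threatening, or intolerability, the study will be terminated". It has no causal condition, but it sets an action and not a recording rule.

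The surrounding design matters for reading this:

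- **Randomised period (Interventional Methods).** Randomisation follows the antibiotics and FMT. Then "One group will consume one bottle of alginate drink twice a day for 8 consecutive weeks, while the other group will take a placebo".
- **Visits (Table 3).** The row "Check of symptoms" is marked at the A-FMT visit, at 4 and 8 weeks, and at 6, 12, 18 and 24 months. Nothing says that these checks feed the adverse-event record.
- **Blinding.** The placebo drink "does not have a different appearance or taste", and the Randomization section states: "The medical staff, assistants and patients of our study team did not know the condition of random allocation until the experiment was completely finished".
- **Endpoints (Outcomes).** No safety endpoint is listed.

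**The concern.** A randomised, blinded comparison settles causality at group level: count every event in each arm and compare. A rule that asks for a causal opinion before an event is counted gives up part of that advantage.

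Case-by-case attribution is least reliable in patients like these. They enter with active disease, and diarrhoea, bleeding or abdominal pain could come from the colitis, the antibiotics, the FMT or the drink. Of the five listed causes, the study drink is the only one that differs between the arms. An effect of alginate therefore reaches the record only if a blinded clinician suspects the drink or another listed cause, and not the disease.

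An article may leave event definitions and collection windows to the full protocol. This is a different matter, because the article states a rule and the rule is restrictive.

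The follow-up clause adds a smaller problem. If it refers to the study treatment, an unresolved event could be closed because the 8 weeks of study drink have ended, although the patient is still seen up to 24 months.

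**Working it through.** **1. The plan's own figure.** There is no safety figure to reproduce. The only power statement concerns the Total Mayo Score: difference 2, SD 2.5, 60 patients allocated 1:1. With d = 2/2.5 = 0.8, 60/2 = 30 per arm and two-sided alpha 0.05 (assumed two-sided), the two-sample t-test gives 86.1%, as stated. This confirms 30 per arm, which is used below.

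**2. What under-recording does when the recorded share is equal.** The event rates and shares here are assumptions. Let the true rates be p1 = 30% and p2 = 15%, and let a share c of events be attributed and recorded in both arms.

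- Recorded difference = c × (30 − 15) percentage points.
- Recorded ratio = (c × 30)/(c × 15) = 2.0 for every c.
- Power = Φ{[|Δ| − 1.96·√(2p̄(1−p̄)/n)] / √([p1(1−p1) + p2(1−p2)]/n)}, with n = 30 and the recorded rates put in for p1 and p2; Δ is their difference and p̄ their mean.

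| Share recorded c | Recorded rates | Difference (points) | Power |
|---|---|---|---|
| 1.00 | 30% vs 15% | 15.0 | 28% |
| 0.75 | 22.5% vs 11.25% | 11.3 | 21% |
| 0.50 | 15% vs 7.5% | 7.5 | 15% |
| 0.25 | 7.5% vs 3.75% | 3.8 | 9% |

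Power is already low at c = 1, because the trial is not sized for safety. The rule makes it lower.

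**3. Less common events.** For an event with an assumed true rate of 5%, the chance of recording at least one case in an arm of 30 is 1 − (1 − 0.05c)^30. This gives 79% at c = 1, 53% at c = 0.5 and 31% at c = 0.25.

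**4. When the recorded share is not equal.** Blinding does not guarantee that background events and events truly due to the drink are attributed equally often. Assume a 20% background rate in both arms and a 30-point excess in one, so the true rates are 50% and 20% (ratio 2.5).

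- Background recorded at 70%, excess at 30%: 14 + 9 = 23% vs 14%, ratio 1.6.
- Background recorded at 30%, excess at 70%: 6 + 21 = 27% vs 6%, ratio 4.5.

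The ratio can move either way. The documents do not show which applies, so no direction of bias can be claimed.

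**The case against.** A reader might infer that the arms cannot be compared fairly, that the comparison leans towards declaring alginate safe, or that UC flares are hidden. The documents support none of these.

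- **Fairness between arms.** Staff and patients are blinded to the end, the placebo is matched, and the same list of causes applies in both arms. With an equal recorded share the ratio is unchanged, as step 2 shows. Step 4 shows that distortion is possible, but its direction is unknown and nothing in the text points to it.
- **Flares.** UC activity is the primary endpoint. It is measured whatever its attribution through the Total Mayo Score and the video-judged colonoscopy at 8 weeks, and symptom checks with blood and fecal samples continue to 24 months.
- **Serious events.** The sentence on these carries no causal condition, and acting on an event requires noticing it.
- **Follow-up.** The end-of-treatment phrase can mean treatment of the event, since the following sentence uses the word treatment in that sense. It also limits follow-up of a recorded event only, and sets no end date for recording new ones.
- **Article format.** A short safety section leaves much to the full protocol.

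These points remove the claims of demonstrated bias and hidden flares. They leave the causal condition in place. Infections and other complaints that are not part of the Mayo score still have no stated route into the record if judged unrelated. Acting on serious events is not a rule for recording all events, and the symptom checks are not linked to the adverse-event record.

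**Conclusion.** The point holds as one about completeness. The stated rule makes the safety record incomplete and dependent on individual judgement, and so lowers the chance of seeing a safety difference between alginate and placebo. The absolute difference shrinks in proportion to the share of events recorded: under the assumed rates of 30% and 15%, from 15 points to between 11.3 and 3.8 points as that share falls from 75% to 25%. These sizes illustrate the mechanism and do not estimate what will happen in this trial, because neither the event rates nor the attributed share is in the documents.

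A bias between arms is not demonstrated, and measurement of UC activity is not affected. The follow-up clause is an ambiguity to be resolved; it is not shown that outcomes will be lost. The wording should be changed, but the primary endpoint does not depend on it.

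**What to change.** Delete the causal condition. Suggested wording: all adverse events will be recorded in both arms irrespective of suspected cause; the blinded investigator's opinion on causality will be entered in a separate field; events starting after randomisation will be compared by arm.

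Also state whether the treatment whose termination ends event follow-up is the study treatment or the treatment of the event, so that an unresolved event is not closed merely because the study drink has ended.

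The cost is a change of wording, one field on the case report form, and somewhat more event reporting at visits that already include a symptom check. The change cannot be applied fully in retrospect. On December 8, 2021, 33 of the planned 60 patients were already included, so at that date full application was possible only for the remaining 60 − 33 = 27 patients, plus the outstanding visits of those already in. The report should say from when the new rule applied and show events under the two rules separately.

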### Progress and Estimated Study Period

This trial began on August 25, 2020. The first study participant was enrolled on September 28, 2020. At present, 33 eligible patients have been included in our study on December 8, 2021. We summarized the baseline characteristics of the 33 patients (Table 4). If the number of participants continues to increase at this pace, this trial is expected to end in October 2022.

**Table 4 T6:** The baseline characteristics of the study participants.

**Items**	**All (*n* = 33)**
Age	40.5 ± 12.0
Sex (M/F)	22/11
Duration of disease (years)	7.3 ± 5.4
**Disease location**	
Proctitis	4
Left-sided colitis	14
Extensive colitis	15
Total Mayo score	7.12 ± 1.9
Mild: 3–5	8
Moderate: 6–10	25
Sum endoscopic mayo score	6.5 ± 4.2
**Ongoing treatment**	
5-ASA	30
Corticosteroid	2
Azathioprine	4
Vedolizumab	1
Anti-TNF	3

*5-ASA, 5-aminosalicylic acid; Anti-TNF, anti-tumor necrosis factor*.

### Sample Size Estimation

In our previous clinical trials (15), ~40 eligible patients with UC were collected in 1 year. Therefore, conservative estimates predict that 60 patients can be collected over 3 years. Eligible patients with UC will be randomized and assigned to two groups with a ratio of 1:1 in a double-blinded fashion. The estimated difference between each group in the Total Mayo Score as the primary endpoint from baseline is −2, and the standard deviation of each group is estimated to be ~2.5. If a two-sample *t*-test is used to test the difference between groups, a power analysis predicts that statistical significance with a power of ~86.1% can be reached.

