## Methods and Analysis

### Study Design and Patients

This double-blinded randomized, placebo-controlled, parallel assignment trial will be conducted at Juntendo University Hospital (Tokyo, Japan). The study will be conducted until December 31, 2024 and is expected to involve 60 patients with UC. Diagnosis of UC will be established based on standard clinical, endoscopic, and histological findings (32) and both hospitalized patients and outpatients will be included. To be eligible, patients must be diagnosed with active UC and meet the requirements of obtaining a Total Mayo Score of 3–10 (7, 9, 10) and a Sum Endoscopic Mayo Score of 2 or above. All patients will be over 20 years old and competent enough to provide informed consent. There are no restrictions on gender.

To ensure the safety of patients, rigorous screening of patients will be performed. If the patient has serious illness, pregnant women, or has received local therapy, etc. will not be included in our experiment. The detailed exclusion criteria for this study are listed in Table 1.

**Table 1 T1:** Exclusion criteria for patients with UC.

Informed consent not provided
Infectious enterocolitis
Receiving local therapy
Serious disease, such as liver disease, kidney disease, heart disease, or other serious complications
Autoimmune disease
Pregnant women and all cases with the possibility of pregnancy
Allergic diseases
Antibiotic therapy in the past 3 months
Any other cases judged inappropriate by the responsible researcher

*UC, Ulcerative colitis*.

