### Outcomes

The primary endpoint is to compare the changes in the Total Mayo Score at 8 weeks after study initiation and A-FMT from baseline between alginate intake group and placebo intake group. The secondary endpoints are the comparison of the following items at 8 weeks after study initiation and A-FMT from baseline:

The change in the Sum Endoscopic Mayo Score.Analysis of intestinal microbiota by 16S rRNA gene amplicon sequencing and whole-genome sequencing.Metabolomic analysis: In addition to SCFAs in stool samples, the amount of lipids, free fatty acids, bile acids, and other clinical markers will also be measured by liquid chromatography tandem mass spectrometry (35).

We will also do same analysis as (1), (2), and (3) at 6, 12, 18, and 24 months after 8 weeks post-study initiation.

Subpopulation analysis of the relationship between patients and donors is considered an exploratory endpoint.

Clinical features will be judged by the Total Mayo Score, and the mucosal appearance of the Mayo Score will be evaluated by endoscopy. To evaluate the overall status of the intestine, endoscopic findings will be evaluated using the Sum Endoscopic Mayo Score, which refers to the sum of the scores of the seven segments (appendicular region, cecum, ascending colon, transverse colon, descending colon, sigmoid colon, and rectum). Intestinal microbial analysis will assess changes in composition and diversity. Metabolomic analysis will evaluate the metabolites of microbiota and elucidate the mechanism of action of alginate in the treatment of UC.

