### Statistical Analysis

Relationships between Total Mayo Scores and Sum Endoscopic Mayo Scores will be assessed using a *t*-test. Furthermore, the correlation between the relative abundance of Bacteroidetes species using a Pearson's correlation coefficient will be evaluated. Differences will be considered significant at *P* < 0.05.

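### The only test named for the change in Mayo score is an unadjusted t-test; adjusting for one named baseline score would be a near-costless gain in precision and robustness

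*Protocol article*

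**What the plan says.** The Outcomes section sets the primary endpoint as a between-group comparison of change: to "compare the changes in the Total Mayo Score at 8 weeks after study initiation and A-FMT from baseline".

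The article mentions a test for the Mayo scores in two places.

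- **Sample Size Estimation** supposes a two-sample t-test in a conditional sentence: "test is used to test the difference between groups". The planned effect is given as "The estimated difference between each group in the Total Mayo Score as the primary endpoint from baseline is −2". For the spread, this section says that "the standard deviation of each group is estimated to be ~2.5", and it puts the power at about 86.1%.
- **Statistical Analysis** names a t-test in a sentence that begins "Relationships between Total Mayo Scores and Sum Endoscopic Mayo Scores will be assessed using a". This is loosely worded: it speaks of relationships between two scores and does not clearly state the comparison of arms. No covariate is named.

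The trial "is expected to involve 60 patients with UC", who are "randomized and assigned to two groups with a ratio of 1:1". On the method of allocation, the Randomization section says "The simple randomization is carried out by the staff in charge"; no stratification is mentioned. Table 3 schedules symptom checks and endoscopy at both screening and the A-FMT visit, and under Interventional Methods randomisation comes after A-FMT. Table 4 gives a baseline Total Mayo Score of 7.12 ± 1.9 and a Sum Endoscopic Mayo Score of 6.5 ± 4.2 in the first 33 patients.

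**The concern.** A change score uses the baseline, but it subtracts it with a coefficient of exactly 1. If the week-8 score rises by less than one point per baseline point, patients who start higher fall further on average, and that predictable part of the change stays in the error term. This is plausible here. Eligibility spans scores of 3 to 10, and a patient who enters at 3 has less room to fall than one who enters at 10. The same holds for the Sum Endoscopic Mayo Score, which adds up seven segments. Table 4 lists 4 patients with proctitis and 15 with extensive colitis, who differ greatly in how much they can improve.

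Two things are at stake. One is precision that could be had from data already collected. The other is the estimate actually obtained: nothing described in the allocation protects balance in the baseline score, so if the arms differ at baseline by chance, a contrast with a fixed slope of 1 is shifted by part of that difference.

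**Working it through.** **Inputs from the article:** difference 2, SD 2.5, 60 patients (30 per arm expected), significance level 0.05, baseline SD s0 = 1.9 (Table 4).

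**Assumptions:** 2.5 is the SD of the change (the natural reading, though not explicit); the test is two-sided; there is no dropout; the week-8 SD s is not given and is varied.

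**Step 1. The plan's own figure.** SE of the contrast = 2.5 × √(2/30) = 0.645. Noncentrality = 2/0.645 = 3.098. With 58 degrees of freedom the noncentral t gives a power of 86.14%. The stated 86.1% is correct.

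**Step 2. What ANCOVA would leave as residual variance.** The variance of change is s0² + s² − 2·cov = 2.5² = 6.25, so:

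- cov = (3.61 + s² − 6.25)/2
- slope b = cov/3.61
- correlation r = cov/(1.9·s)
- residual variance = s²(1 − r²)
- ratio to the change-score variance = residual variance/6.25

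Estimating the slope costs an expected factor of 1 + 1/(60 − 4) = 1.018 in variance and one degree of freedom (57 left).

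Worked for s = 2.5: cov = 3.61/2 = 1.805; b = 0.50; r = 1.805/4.75 = 0.38; residual variance = 6.25 × (1 − 0.1444) = 5.35; ratio = 0.856.

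| Assumed week-8 SD | Slope b | r | Variance ratio before slope cost | Power, slope cost included |
|---|---|---|---|---|
| 1.9 | 0.13 | 0.13 | 0.57 | 98.0% |
| 2.25 | 0.34 | 0.28 | 0.75 | 93.8% |
| 2.5 | 0.50 | 0.38 | 0.86 | 90.4% |
| 3.0 | 0.88 | 0.56 | 0.99 | 85.8% |
| 3.14 (= √9.86) | 1.00 | 0.61 | 1.00 | 85.5% |

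The last row is the worst case: 86.1 − 85.5 = 0.6 percentage point lost. Break-even is where the correlation between change and baseline is about 0.13 in absolute value; below that, ANCOVA is marginally less precise at this sample size.

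**Step 3. Chance imbalance.** SE of the baseline difference = 1.9 × √(2/30) = 0.49. The probability that it exceeds 0.5 point in either direction is 2 × P(Z > 0.5/0.49) ≈ 0.31.

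**Step 4. What such a gap does.** Given a 0.5-point baseline difference, the change contrast is shifted by (1 − b) × 0.5:

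- s = 2.5: 0.50 × 0.5 = 0.25 point, one eighth of the planned effect of 2 and 0.25/0.645 = 0.39 of the contrast's SE.
- s = 3.0: 0.12 × 0.5 = 0.06 point.

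No matching calculation is possible for the Sum Endoscopic Mayo Score, because the article gives no SD of change for it.

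**The case against.** The strongest reply is that nothing here is wrong. A t-test on change between randomised arms is unbiased over randomisations and holds its type I error, and its power is correctly stated. The sentence in Sample Size Estimation is conditional; sizing on an unadjusted test and adjusting in the analysis is common and usually conservative. A full protocol or analysis plan that is not shown may already specify adjustment. The possible gain also depends on a week-8 SD that appears nowhere in the article, and it combines an SD observed in 33 patients with a planning guess of 2.5. The 98% figure needs a baseline to week-8 correlation of only 0.13.

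Most of this stands, and it limits the point. A reader might infer several stronger things that the document does not support:

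- *That the t-test ignores the baseline.* It does not; it subtracts it. What is missing is an estimated slope.
- *That the planned result would be biased.* The shift in Step 4 is conditional on an observed imbalance, goes either way, and averages to zero.
- *That ANCOVA is never less precise.* With a slope near 1 it is slightly less precise at 60 patients.
- *That ANCOVA removes chance imbalance.* It adjusts only for the baseline score, not for other differences between arms.

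What the reply does not remove is that the Statistical Analysis section is not conditional, names only a t-test for these scores, and does not clearly state the primary comparison. It needs rewording in any case, and the better model can be put in at the same time.

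**Conclusion.** The point holds as a recommended improvement, not as an error. For a change-from-baseline endpoint under simple randomisation of about 60 patients, the article names only an unadjusted test, although a baseline score is collected before randomisation. The trade is lopsided: at worst 0.6 percentage point of power is lost, against gains of about 4 points (week-8 SD 2.5) to 12 points (week-8 SD 1.9). Adjustment also protects against a baseline gap above 0.5 point, which has about a 31% chance.

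The size of the gain rests on reading 2.5 as the SD of change, on a baseline SD of 1.9 from the first 33 patients, and on the assumed week-8 SD. The small downside and the 31% need no week-8 SD.

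**What to change.** Before unblinding, state in the Statistical Analysis section:

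1. The primary analysis is ANCOVA of the week-8 Total Mayo Score on arm, adjusted for one named pre-randomisation baseline Total Mayo Score, reporting the adjusted difference with its 95% CI. Using the change as the outcome, with the same covariate, gives the same treatment estimate.
2. Which visit supplies that baseline. Screening and the A-FMT visit both precede randomisation, and the endpoint wording does not settle which is meant.
3. The same model applies to the Sum Endoscopic Mayo Score, with its own baseline.
4. The unadjusted t-test on change is kept as a sensitivity analysis.

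The cost is a few sentences and one degree of freedom. It needs no new data, visits or patients, and the sample size statement can stand as it is. The power figures above are for a single covariate; adding a second baseline score would cost a further degree of freedom, and any gain from it has not been quantified here.
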